### Safety evaluation

2.13

Safety evaluations were performed according to the National Cancer Institute’s Common Terminology Standard for Adverse Events (CTCAE v.5.0), and patient adverse events were monitored every 3 months from baseline to disease progression, death, or 2 years after surgery. The evaluation methods included routine blood tests, urine tests, biochemical tests, and electrocardiography.

### Data collection and management

2.14

Patients will undergo periodic follow-up (once a month during the treatment period and once every 3 months during the follow-up period, including electronic questionnaires or telephone follow-up). After surgery, they will be observed for at least 3 years. Data on vital signs, physical examination, weight, height, body surface area, BMI, ECOG score, KPS score, QLQ-STO22, MDASI-GI, PGSAS-45, peripheral blood inflammatory indicators, blood and urine routine, complete biochemical tests, electrocardiogram, and blood tumor markers will be collected for each treatment cycle and during follow-up visits every 3 months. For participants who did not experience disease progression after completing six courses of treatment, imaging follow-up was conducted every 3 months for 2 years post-surgery and then every 6 months after that until disease recurrence or initiation of alternative therapies. The basic information of the patients and the relevant information required for the study will be recorded in the CRF. Only authorized researchers, representatives of research-undertaking units, ethics committees, and higher-level management departments can access patient records upon reasonable request. No public reports of the results of this study disclose the patient’s name or identity. The research team will protect the privacy of the patient’s medical data as much as possible within the scope permitted by law.

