### Sample size

2.11

This was a randomized controlled trial. The primary outcome was the 2-year disease-free survival (DFS) rate of patients with GC after surgery. It was estimated that the DFS rate 2 years after surgery in the control group was 43.9%, whereas the DFS rate in the intervention group was 63.9%. For α = 0.05 (bilateral), β = 0.2. Assuming that the enrollment rate of the study patients remained unchanged, the proportion of the intervention group to the control group was 1:1. The sample size for N1 was 96 cases in the intervention group, and for N2 was 96 cases in the control group, as calculated using the PASS 11 software. However, a detachment rate of 10% must be considered in the research process. Therefore, the intervention and control groups comprised 106 patients each (212 patients total).

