#### Primary outcome

2.12.1

The primary outcome of this study is the 2-year DFS rate after surgery, which refers to the proportion of patients who have not experienced recurrence, metastasis, or (for any reason) death within 2 years after surgery.

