### Statistical analysis and method

2.16

SAS 9.4 statistical software will be used, and full analysis set (FAS) and protocol compliance set (PPS) analyses will be performed on the efficacy indicators. A safety dataset analysis should be conducted for adverse reactions. All statistical tests will be conducted bilaterally, and statistical significance will be set at *p* ≤ 0.05. We will analyze whether there are outliers in the data and conduct a professional analysis of outliers to decide whether to accept or reject them. After this, we will analyze the data for missing values and conduct a professional analysis to determine whether the missing values are listed as missing or data transferred. The proportion of shedding cases should not exceed 10%; otherwise, analysis and explanation should be provided. The measurement data were described as mean, standard deviation, median, minimum, and maximum whereas counting data were described as frequency, percentage, etc. Quantitative data analysis will be performed using *t*-tests, rank-sum tests, etc. Counting data analysis will be performed using chi-square tests, ridit analyses, etc. Survival data analysis will be performed using the Kaplan–Meier method, Wilcoxon rank sum test, or log-rank test. A Cox-proportional risk regression model was used for multivariate survival analysis.

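### Section 2.14 ties post-treatment recurrence imaging to completing six courses and Table 1 does not, so 24-month recurrence status is not secured for patients who stop early

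*Protocol article*

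**What the plan says.** The primary outcome (section 2.12.1) is "the proportion of patients who have not experienced recurrence, metastasis, or (for any reason) death within 2 years after surgery". For the analysis populations, section 2.16 states that "full analysis set (FAS) and protocol compliance set (PPS) analyses will be performed on the efficacy indicators".

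The imaging rules stand in two places:

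- **Section 2.14 (text).** "For participants who did not experience disease progression after completing six courses of treatment, imaging follow-up was conducted every 3 months" up to two years after the operation and six-monthly from then on, "until disease recurrence or initiation of alternative therapies". No schedule is given for patients who stop before the sixth course, and the therapies that end imaging are not defined.
- **Table 1 (section 2.12).** PET-CT/CT/X-ray is marked mandatory at baseline, at the fourth visit (days 84–91), at the Nth visit and at follow-up visits, which are three-monthly. No condition on courses completed is attached, and there is no change of interval after two years.

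Two other sections bear on patients who stop early. Sections 2.6 and 2.10 list poor compliance, inability to adhere and the patient's own request among the grounds for withdrawal or discontinuation. Section 2.10 states follow-up of outcomes only for those who stop because of serious adverse events. Section 2.14 does plan three-monthly contact and at least three years of observation after surgery for patients in general, but allows that contact to be by electronic questionnaire or telephone.

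**The concern.** Completing six courses happens after randomisation and can depend on the assigned treatment through tolerability, taste or perceived benefit. If the scans that find recurrence depend on it, ascertainment of the primary event depends on adherence. A patient who stops at course two still belongs to the full analysis set in its usual sense. Under the text of section 2.14 that patient has no stated scan series, and a telephone call will not find an asymptomatic recurrence.

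With a proportion as primary outcome, a missed recurrence is likely to be counted as disease-free. Equal loss in both arms overstates disease-free survival (DFS) and shrinks the difference. Unequal loss can produce a difference in either direction when there is none.

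The alternative-therapies stop raises a related problem. New therapy may begin because recurrence is suspected, and assessment would end at that moment.

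**Working it through.** **1. The plan's own figure.** Section 2.11 states that "the DFS rate 2 years after surgery in the control group was 43.9" (per cent) and "the DFS rate in the intervention group was 63.9" (per cent). "For α = 0.05 (bilateral), β = 0.2", and "the proportion of the intervention group to the control group was 1:1". With mean proportion 0.539, the usual two-proportion formula gives

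n = [1.96 × √(2 × 0.539 × 0.461) + 0.842 × √(0.439 × 0.561 + 0.639 × 0.361)]² / 0.20² ≈ 96.3, or 97 per arm.

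The plan has 96, where power is 79.9%. The sample size reproduces and is not in question. With all 106 enrolled per arm analysed and every event seen, power is Φ[(0.20 − 1.96 × 0.0685)/0.0671] ≈ 84%.

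**2. How much of the two-year window depends on post-treatment imaging.** Entry is at most 8 months after surgery (section 2.4). Six courses of 4 weeks (section 2.8) are 24 weeks, or 168/30.44 = 5.5 months. The latest entrant finishes at 8 + 5.5 = 13.5 months, which leaves 24 − 13.5 = 10.5 months. Earlier entrants have longer.

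**3. The two imaging rules side by side.**

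| Question | Section 2.14 text | Table 1 |
|---|---|---|
| Who is scanned after treatment | Progression-free patients who completed six courses | Anyone attending follow-up visits |
| Interval after two years | Six-monthly | Three-monthly |
| Stop | Recurrence or alternative therapies | None stated |

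Table 1 does not say whether patients withdrawn under sections 2.6 or 2.10 keep attending follow-up visits.

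**4. Illustration of size.** Assumptions that are not in the document: a fraction q of an arm stops early, these patients have the same event risk as the rest, and a share u of their two-year events is missed and counted as disease-free. For true DFS p,

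observed DFS = 1 − (1 − p)(1 − q·u).

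*No true effect (p = 0.439 in both arms), q = 10% on placebo and 20% on YWJP:*

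- u = 0.5: placebo 1 − 0.561 × 0.95 = 46.7%; YWJP 1 − 0.561 × 0.90 = 49.5%; difference 2.8 points.
- u = 1: placebo 1 − 0.561 × 0.90 = 49.5%; YWJP 1 − 0.561 × 0.80 = 55.1%; difference 5.6 points.

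At 106 per arm, the chance of a significant result favouring YWJP rises from the nominal 2.5% to about 6% and 13% respectively. If the stopping rates are swapped, the bias favours placebo.

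*Planned effect, equal stopping, 106 per arm analysed:*

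| q in both arms | u | Placebo | YWJP | Difference | Power |
|---|---|---|---|---|---|
| 10% | 0.5 | 46.7% | 65.7% | 19.0 points | 80% |
| 20% | 0.5 | 49.5% | 67.5% | 18.0 points | 76% |
| 20% | 1 | 55.1% | 71.1% | 16.0 points | 68% |

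**5. No scan fixed at month 24.** Patients enter at varying times after surgery, so a three-monthly series that starts after course six need not land on month 24. Assume exponential event times and 17 months at risk to month 24 (neither is in the document). A last scan 1.5 to 3 months early then moves S(17 − g) − S(17) past the cut-off. That is 3.3 to 6.9 points on placebo and 2.6 to 5.3 on YWJP. The lag affects both arms, so the between-arm effect is only 3.3 − 2.6 = 0.7 to 6.9 − 5.3 = 1.6 points.

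**The case against.** The strongest reply is Table 1. It makes imaging mandatory during treatment and at every three-monthly follow-up visit without regard to courses taken. The sentence in section 2.14 can then be read as saying when post-treatment imaging begins, not who is left out. This stands against the stronger inference that imaging is defined only for completers and that recurrence in the others goes unobserved. Deaths count as events, survival status is mandatory at every visit, and clinically evident recurrences can be reported at the three-monthly contacts. Patients who stop because of recurrence already have their event. The supportable statement is that recurrence may be missed or detected late.

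A reader might also infer that starting alternative therapy censors the primary outcome informatively. The document does not support that. The primary outcome is a proportion, no censoring rule is stated, and the stop can be read as belonging only to the six-monthly phase after two years. On that reading it leaves the two-year rate alone and touches only DFS time and the three-year recurrence rate.

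Finally, the stopping rates used above have no source. The only related planning figure is the 10% dropout allowance, and at 10% in both arms with half of the events missed, power is still 80%.

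What the reply does not remove is the conflict. The text and the table give sites two rules, the text omits early stoppers, and follow-up after stopping is stated for one reason only. An analysis plan cannot recover scans that were never taken.

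**Conclusion.** The concern holds as a conflict and a gap in ascertainment. Sections 2.14 and Table 1 disagree on who is imaged after treatment, for how long and at what interval. Together with sections 2.6 and 2.10, they leave recurrence status to month 24 unsecured for patients who stop early, although the primary outcome needs it.

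The size of the bias cannot be computed from the document. The 2.8 to 5.6 points under no true effect are 14% to 28% of the planned 20-point difference (2.8/20 and 5.6/20). They rest on assumed stopping of 20% against 10%, and 5.6 is an upper bound because it requires every event among early stoppers to be missed. Equal stopping mainly costs power, down to 68% in the worst case shown. The absence of a fixed month-24 scan mostly overstates DFS in both arms and adds little to the difference between them.

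**What to change.** Reconcile section 2.14 with Table 1, including the imaging interval after two years, and make these changes:

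1. State who is imaged. Suggested wording: *The planned recurrence imaging continues for all randomised patients to at least 24 months after surgery, regardless of the number of courses taken or of any new therapy, until recurrence, death or withdrawal of consent to follow-up.*
2. Place one of the scheduled three-monthly scans at month 24 after surgery.
3. Delete the alternative-therapies stop, or define the term and state whether the stop applies before or only after two years.
4. In sections 2.6 and 2.10, separate stopping study treatment from leaving follow-up, so that outcome assessment continues after discontinuation for any reason, not only after serious adverse events.

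The cost is protocol wording and a small number of additional scans, on the existing schedule, in patients who stop early. No new procedure is needed.

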### Recruitment

2.2

We plan to recruit patients from seven traditional Chinese oncology hospitals nationwide, led by Guang’anmen Hospital, and enroll patients by following up with expert clinics, playing recruitment advertisements on hospital LED screens, and posting recruitment posters. When we encounter potential patients, we will introduce our study protocol, including the objectives, intervention methods, processes, and potential adverse reactions. The research team will conduct repeated screenings of patients on a two-person basis. Patients who meet the inclusion criteria and wish to voluntarily participate in the study will sign an informed consent form.

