### Inclusion criteria

2.4

1. Research cases must be sourced from real-world registration platforms.2. Stage II–III non-esophageal gastric junction GC that meets the diagnostic criteria and does not indicate tumor recurrence or metastasis by imaging.3. Patients with GC who underwent radical gastrectomy (R0) within 8 months after surgery and completed at least six cycles of adjuvant chemotherapy with standard regimens (XELOX and SOX).4. Eastern Cooperative Oncology Group (ECOG) performance status score of 0–2.5. Patient ages ranging from 18 to 75 years, with no sex limitations.6. Expected survival time ≥3 months.7. Patients who voluntarily participated in the study, signed an informed consent form, and participated in the follow-up.

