### Intervention

2.8

The intervention group will receive YWJP, whereas the control group will receive YWJP placebo. Patients will take one pack each time, dilute it with boiling water, and administer it twice daily (in the morning and evening). The course of treatment will be 4 weeks, and six courses are planned.

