### Criteria for adherence

2.9

After enrollment, patients will take their medication according to the method described in the “intervention” section. During the intervention, symptoms such as nausea, vomiting, liver and kidney dysfunction, diarrhea, and infection will be treated with medication. However, specific symptoms and combined medications must be recorded. Receiving modern antitumor treatment (including chemotherapy, immunotherapy, molecular targeted therapy, and radiotherapy) or taking other Chinese herbal decoctions, Chinese herbal injections, and traditional Chinese patent medicines with antitumor effects during the intervention will be prohibited.

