### Outcome measurements

2.12

The 2-year DFS rate as the primary outcome and DFS, OS, 1- to 3-year cumulative recurrence and metastasis rate, and 1- to 3-year cumulative survival rate as the secondary outcome will be calculated at the end of follow-up. The lymphocyte count-to-monocyte count ratio (LMR) (59), lymphocyte count-to-neutrophil count ratio (LNR) (60), prognostic nutritional index (PNI) (61), Quality of Life Questionnaire of Stomach 22 (QLQ-STO22) (62), M. D. Anderson Symptom Assessment Scale Gastrointestinal Tumor Specific Module (MDASI-GI) (63), Postgastrectomy Syndrome Assessment Scale-45 (PGSAS-45) (64) (diagnosis of the syndrome should refer to the 2014 *Guidelines of Diagnosis and Therapy in Oncology with Traditional Chinese Medicine*), and other secondary outcome indicators will be collected at weeks 0–6, whereas the total fat area (TFA) (65), visceral fat area (VFA) (66), subcutaneous fat area (SFA) (67), visceral adiposity index (VAI) (68), and tumor markers will be collected at weeks 0, 3, and 6. All measurement results will be recorded in the case report form (CRF). The details of outcome measurement projects are shown in **Table 1**.

**Table 1 T1:** Treatment stage flowchart.

Item		Baseline	Treatment observation				Follow-up
Number of visits		1st time	2nd time	3rd time	4th time	*N*th time	*N* + *X*th time
Observation time		Days −7 to 0	Days 28–35	Days 56–63	Days 84–91	End of *N*th treatment course	Once every 3 months
Inclusion/Exclusion criteria		√					
Sign informed consent form		√					
Collect medical history							
Demographic data		√					
Diagnosis and TNM classification		√					
Past history and comorbidities		√					
Clinical observation							
Vital signs		√	√	√	√	√	√
Physical examination		√	√	√	√	√	√
Survival situation		√	√	√	√	√	√
MDASI-GI		√	√	√	√	√	√
Tongue and pulse condition		√	√	√	√	√	√
TCM syndrome		√	√	√	√	√	√
Imaging examination	PET-CT/CT/X-ray	√			√	√	√
	MRI, B-mode ultrasonography	*	*	*	*	*	*
	Bone scanning	*	*	*	*	*	*
	Gastroscope	*	*	*	*	*	*
Tumor marker		√	*	*	√	*	*
Indicators related to fat distribution		√	*	*	√	*	*
QLQ-STO22		√	√	√	√	√	√
PGSAS-45		√	√	√	√	√	√
Safety observation							
Blood routine		√	√	√	√	√	√
Hepatic and renal function		√	√	√	√	√	√
Urine and stool routine		*	*	*	*	*	*
Electrocardiogram		√	√	√	√	√	√
NCI adverse reaction			√	√	√	√	√
Adverse event			√	√	√	√	√
Other work							
Efficacy evaluation			√	√	√	√	√
Drug combination			√	√	√	√	√

*This check is optional.

√ This check is necessary.

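### The stated stop for imaging when another therapy begins can end the search for recurrence in patients who are still recurrence-free; whether it also applies before the 2-year primary time point is left unclear

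*Protocol article*

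**What the plan says.** - **Imaging rule (2.14).** For participants without progression after six courses, imaging runs "every 3 months for 2 years post-surgery and then every 6 months after that until disease recurrence or initiation of alternative therapies". The same section says of patients "After surgery, they will be observed for at least 3 years", and allows follow-up by electronic questionnaire or telephone.
- **Visit grid (2.12, Table 1).** PET-CT/CT/X-ray is ticked in the 3-monthly follow-up column. The legend for the tick is "This check is necessary". No stop for new therapy is shown.
- **Primary outcome (2.12.1).** It is "the proportion of patients who have not experienced recurrence, metastasis, or (for any reason) death within 2 years after surgery". New therapy is not part of the definition. Nor is it part of DFS time or the 1- to 3-year recurrence rates in 2.12.2.
- **Concomitant treatment (2.9).** Modern antitumour treatment, other herbal decoctions and injections, and "traditional Chinese patent medicines with antitumor effects during the intervention will be prohibited". The ban is tied to the intervention period.
- **Timing (2.8, 2.4).** "The course of treatment will be 4 weeks, and six courses are planned". Eligible patients are those who "underwent radical gastrectomy (R0) within 8 months after surgery".
- **Setting (2.2).** "We plan to recruit patients from seven traditional Chinese oncology hospitals nationwide".

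**The concern.** The two stops are joined by "or", so the second has effect only in patients who have not recurred. Those are the patients in whom recurrence still has to be looked for. A patient who begins another herbal prescription after the study courses loses the scheduled scans. A later silent recurrence is then found late or not at all, and the patient is counted as disease-free or becomes missing. No analysis plan can recover scans that were never taken.

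The stop could well be used. The ban on other antitumour medicine lapses when study treatment ends, patients come from traditional Chinese oncology hospitals, and the article calls its own prescription complementary and alternative medicine. Starting another therapy may also depend on symptoms, which the study drug is meant to change, so the loss of scans need not be equal between arms. Equal loss dilutes the effect. Unequal loss biases it, in either direction.

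**Working it through.** **1. How far the stop reaches.** There are two readings of the sentence in 2.14.
- *Narrow:* the 3-monthly phase has its own limit (2 years after surgery), and the stops govern only the 6-monthly phase. The 2-year rate is untouched. DFS time and the 3-year recurrence rate are affected.
- *Whole schedule:* imaging would naturally end at recurrence in either phase, and the other-therapy stop shares that clause. The primary outcome is then affected too.

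Steps 2 to 5 apply only to the whole-schedule reading.

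**2. Exposed period.** Six 4-week courses are 24 weeks = 168/30.44 = 5.52 months. With entry at month 8, treatment ends at 8 + 5.52 = 13.5 months after surgery, leaving 24 − 13.5 = 10.5 months. With entry at month 4 (my assumption for an early entrant) the gap is 14.5 months.

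**3. The plan's own figure (2.11).** Rates 0.439 and 0.639, two-sided 5%, power 80%, pooled null variance:
n = [1.960·√(2·0.539·0.461) + 0.842·√(0.439·0.561 + 0.639·0.361)]² / 0.20² = 96.3 per arm. The plan states 96, so it is reproduced. Power at 96 per arm is 79.9%.

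**4. Events in the exposed period.** Assume a constant hazard from randomisation: S(t) = exp[ln(S2)·t/(24 − entry)], where S2 is the 2-year rate. The share of patients with an event between week 24 and month 24 is L = S(5.52) − S2.
- Entry month 8: control 0.7528 − 0.439 = 0.3138; YWJP 0.8568 − 0.639 = 0.2178. Times 106: 33.3 + 23.1 = 56.4 events.
- Entry month 4: 0.3578 and 0.2447, giving 63.9 events.
- All primary events: 106·(0.561 + 0.361) = 97.7.

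So 56–64 of about 98 events fall in the gap (43–50 with Weibull shape 0.7, 72–79 with shape 1.5).

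**5. Effect on the comparison.** A share q starts another therapy if still event-free (no figure in the article; 10–30% assumed), and a share m of their later events is missed and counted as disease-free.
- *All start at week 24:* observed rate = S2 + q·m·L.
- *Starts spread evenly over the gap:* replace L by the average of S(u) − S2 over the gap, G = L/(λ·gap) − S2, with λ = −ln(S2)/(24 − entry). Entry month 8, control: λ = 0.0515, λ·gap = 0.539, G = 0.3138/0.539 − 0.439 = 0.143. YWJP: G = 0.104.

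Example, entry month 8, q = 20%, m = 1, spread starts: 0.439 + 0.2·0.143 = 0.468 and 0.639 + 0.2·0.104 = 0.660, a difference of 19.2 points and power 77%.

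Power at 96 per arm (base 80%); ranges cover entry at month 4 to 8:

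| Uptake, control v YWJP | Spread, all missed | Spread, half missed | Week 24, all missed | Week 24, half missed |
|---|---|---|---|---|
| 10% v 10% | 78% | 79% | 76% | 78% |
| 20% v 20% | 77% | 78% | 71–73% | 76% |
| 30% v 30% | 75–76% | 77–78% | 67–69% | 73–74% |
| 30% v 10% | 63–65% | 72–73% | 38–44% | 60–63% |

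With no true effect (both rates 43.9%) and uptake 10% control v 30% YWJP, at 106 per arm:
- Spread starts: a false advantage of 2.9–3.2 points and two-sided error 7–8% (half missed: 1.4–1.6 points, 5.5–5.6%).
- All at week 24: 6.3–7.2 points and 15–18% (half missed: 3.1–3.6 points, 7–8%).

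**The case against.** A reader might infer that 2.14 definitely ends imaging before 2 years and so biases the primary outcome. The text does not support that. The 3-monthly phase carries its own end point, and the stops follow the 6-monthly phase, which otherwise has no end. The sentence is also already limited to patients without progression. This objection stands: a stop before 2 years is a possible reading, not an established one.

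Other points for the plan:
- *Table 1 is only a visit grid.* It shows no stop at recurrence and no change to 6-monthly imaging either, so its silence on new therapy is weak evidence of a contradiction. That is fair. Still, it marks the scan as necessary, so the two places do not give sites the same instruction.
- *The term for other therapies is undefined.* It may mean replacement anticancer treatment, and the Discussion says guidelines recommend only watchful waiting for recurrence-free patients. True, but nothing in the article excludes herbal medicine.
- *Other detection continues.* Sections 2.12 and 2.14 keep 3-monthly contact, examination, survival status and at least 3 years of observation, and a symptomatic patient would probably be scanned anyway. So missing every later event is an extreme case. Silent recurrence remains the gap.
- *The largest losses need unlikely conditions:* every start at week 24, no other detection, or threefold unequal uptake in a double-blind trial. This stands, and the spread-start figures are the fairer guide.
- *Handling of new therapy belongs in the full protocol or analysis plan.* That is true of censoring rules, but not of a stated rule that ends data collection.

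**Conclusion.** The concern holds in limited form. It is certain that 2.14 makes the start of another therapy a reason to stop imaging in recurrence-free patients, and that no outcome definition makes that exception. The least consequence is lost detection for DFS time and the 3-year recurrence rate.

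An effect on the 2-year primary outcome depends on the whole-schedule reading. Even then it is modest under reasonable assumptions: with equal uptake of 10–30% and starts spread over the gap, power is about 75–79% instead of 80%. The 67–76% range needs all starts at week 24 and every later event missed. Unequal uptake could bias the result in either direction, but blinding makes a large imbalance unlikely.

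These sizes rest on the plan's own DFS rates, a constant hazard, entry 4–8 months after surgery, and uptake shares that the article does not give. The label is a cheap improvement.

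**What to change.** In 2.14, delete the second of the two stops. State that imaging continues every 3 months to 2 years after surgery, then every 6 months, in all randomised patients until recurrence, death or end of follow-up, whether or not six courses were completed and whatever other therapy is started. Align Table 1 with this. Record the start date of any other antitumour therapy, including Chinese medicine, and add a sensitivity analysis that censors at that date.

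Cost: one sentence, one table column and one recorded date. No scans are added beyond Table 1. Compared with the whole-schedule reading of 2.14, a patient who starts another therapy at week 24 gains about 3–4 scans up to 2 years (10.5/3 to 14.5/3, rounded down), and up to two more by year 3. Later starters gain fewer. With 171–178 patients expected to be event-free at week 24, uptake of 10–30% means about 17–53 patients. The downside is that events after the switch also reflect the other therapy, which the sensitivity analysis addresses.
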